### Outcomes

#### Primary outcome

##### Objective walking capacity

Walking capacity will be assessed using the SPWT. The test requires subjects to walk on a level surface without support at their own pace until forced to stop due to symptoms of LSS or a time limit of 30 min [43]. Test termination will be defined as a complete stop of 3 s. A blinded assessor will follow one metre behind the subject, without conversing, with a distance instrument (Lufkin Pro-Series Model PSMW38), and stopwatch. Distance walked and time to test termination will be recorded. The SPWT is considered the gold standard with high validity for assessing walking capacity in this population since it directly observes walking ability under conditions representative of a real world setting [31, 44]. It has high test-retest reliability (ICC = 0.98) [43]. The minimal clinically important difference (MCID) in walking distance in this population is unknown.

#### Secondary outcomes

##### Physical function

This will be measured using the physical performance scale of the Zurich Claudication Questionnaire (ZCQ) also known as the Swiss Spinal Stenosis Scale. The ZCQ is a validated condition-specific measure consisting of three scales; a physical performance scale, a symptom severity scale and a patient satisfaction scale [45, 46]. The physical performance scale consists of five questions related to walking ability. The mean un-weighted score will be calculated. The scale has a high internal consistency with a Cronbach’s coefficient of 0.91, a test-retest reliability correlation coefficient of 0.82 and a responsiveness of 1.07 using the standardized mean [45, 46]. The MCID has been estimated to be 0.5 [45].

##### Symptom severity

This will be measured using the symptom severity scale of ZCQ. The symptom scale consists of seven questions pertaining to overall severity of pain, pain frequency, back pain and, pain in the leg, numbness, weakness and balance disturbance. The scale has a high internal consistency with a Cronbach’s coefficient of 0.87, a test-retest reliability correlation coefficient of 0.92 and a responsiveness of 0.86 using the standardized mean [45, 46]. The MCID is estimated to be 0.5 [45].

##### Functional disability

Functional disability will be measured by the Oswestry Disability Index (ODI) [47]. The ODI is a reliable and validated measure of back-related disability where 0 represents no disability and 100 represent the worse possible disability. We will also record separately the score of the walking section (ODI walk) of the ODI. The ODI walk score has been shown to be highly correlated to objective walking distance (*r* = 0.83). The MCID for the ODI is 8–12 percentage points [48].

##### Leg and back pain intensity while walking

Leg and back pain intensity while walking will be independently measured at baseline and at each follow-up with the 11-point numerical rating scale (NRS). The NRS is a global measure of pain intensity anchored by two extremes of pain intensity ranging from 0 (referring to “No pain”) to 10 (referring to “Pain as bad as it could be”). The NRS has good short-term test-retest reliability with correlation coefficients ranging from 0.95 to 0.99 when re-administered within 24 h [49]. The NRS has good construct validity and can distinguish between various levels of pain in subjects with chronic post-operative pain [49, 50].

##### Health-related quality of life (H-RQoL)

We will use the Medical Outcomes Study Short-Form Health Survey version two (SF-36) to measure health-related quality of life. The SF-36 has 36 items that measure the H-RQoL of a subject. Two summary scores can be computed: the physical component score and the mental component score. The questionnaire has been shown to have excellent reliability demonstrated with internal consistency and test-retest methods. The SF-36 is a valid and reliable measure for clinical and general populations with a reported intra-class correlation coefficient of 0.85 [51].

##### Co-morbidity scale

We will use the validated and reliable 18-item Co-Morbidity Disease Index that has an emphasis on functional activity [52].

##### Depressive symptomatology

Depressive symptomatology in the previous week will be measured with the Center for Epidemiological Studies-Depression Scale (CES-D). The CES-D is a widely used 20-item self-report scale designed to measure current level of depressive symptomatology in population-based epidemiologic research [53]. It has good test-retest reliability and internal consistency and possesses good factorial and discriminate validity [54]. The CES-D is scored from 0 to 60 with higher scores indicating greater depressive symptomatology [53].

##### Lower extremity function and balance

The Short Physical Performance Battery (SPPB) will be used as an objective assessment of lower extremity function and balance [32]. The SPPB is a collection of timed physical tests including standing balance (tandem, semi-tandem, side by side), 4-m walk and repeated sit-to-stand from a chair. The examination requires 10–15 min to complete on average. The overall score on the SPPB is strongly correlated with current self-reported disability highly predictive of future disability among community dwelling older persons [32]. The individual physical tests making up the SPPB have high inter-rater reliability (kappa = 0.80–1.0) and summary scales have been shown to have good to excellent test-retest reliability (kappa = 0.99) [32, 55]. The internal consistency of the summary scale is adequate (Crochbach’s alpha = 0.76) [56].

##### Fear of falling

Fear of falling is a significant predictor of future falls and can be assessed using the Falls Efficacy Scale (FES). The FES assesses patients’ perception of balance and stability during usual activities of daily living [57, 58]. The test-retest reliability is adequate within the geriatric population (*r* = 0.71) and the instrument has excellent internal consistency (Cronbach’s alpha = 0.91) [57]. Furthermore, scores on the FES have been shown to be moderately to highly correlated with other measures of balance confidence (*r* = 0.55–0.86) [59].

##### Co-interventions

We will measure co-interventions by asking participants to self-report the type and frequency of consultations with other health care providers and the type of interventions received beyond those provided in the trial. This would include physiotherapy, chiropractic, massage therapy, acupuncture, epidural injections and surgery. We will also ask participants if they have used medications and the frequency of use for their back and/or leg symptoms.

##### Compliance

At each treatment visit and each follow-up assessment, we will ask participants about their compliance with their self-management programs (Groups 1 and 2). We will ask how often they are performing their exercises, body alignment techniques and self-management strategies. We will also assess compliance from the weekly exercise diary located in the instructional workbook.

### Statistical Issues

#### Sample size

For the primary RCT we have estimated the sample size for the primary outcome of objective walking capacity based on an estimate of the difference in the proportion of participants who achieve a MCID in walking distance. Since the MCID for the SPWT is unknown we will estimate it to be an improvement in walking distance from baseline of 30 % or more. We estimate a total of 30 % of participants will achieve the estimated MCID in Group 2 and 60 % in Group 1. Based on an estimate of 30 % difference in proportions, a power of 0.8, an alpha of 0.05 and an estimated drop-out rate of 20 %, a minimum of 52 participants per group is estimated to be required to achieve significance using a two-tailed *t*-test for two independent proportions [60]. Our primary end point will be the 6-month follow-up.

#### Statistical analysis

Baseline status of treatment groups will be compared using two-tailed independent samples t tests, Chi squared tests of independence, and Mann-Whitney U tests as indicated. Our analyses will be based on the “intention to treat” principle. Data will contain repeated measurements of the main response variables.

We will analyze the primary outcome (SPWT) by calculating the differences in proportions meeting the MCID using Pearson Chi Squared test with 95 % confidence intervals. To control for potential confounding (sex, education, perceived health status, dominant leg or back pain, and hospital), logistic regression models and generalized estimation equation (GEE) methods will be used [5]. These models will control for baseline differences not balanced by randomization. Dichotomous secondary outcomes will be analyzed similarly.

For continuous secondary outcomes we will first compute the group-specific mean, standard deviation and median at each follow-up interval. Second, we will build ordinary least-square (OLS) models using generalized estimating equation to account for the autocorrelation present in the outcomes [5]. Third, we will test whether the group effects are constant throughout the follow-up periods [5]. Fourth, we will test whether imbalances in the distribution of the baseline covariates confound the group effects. Covariates added to the crude linear model that change any of group regression coefficients by 10 % percent or more will be retained as confounders in the adjusted models [61]. The group effects will be reported as the mean differences and 95 % for each follow-up interval.

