### Source population

Eligible participants are individuals who consult with specialists (orthopedists, neurosurgeons, rheumatologists, neurologists or physiatrists), family physicians or chiropractors for symptoms suggestive of neurogenic claudication at one of seven hospitals and several community clinics in Toronto, Canada and the surrounding area.

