### Recruitment

Participating physicians and chiropractors will identify potential participants using an eligibility checklist (Table 1). Eligible potential participants will be given a pamphlet outlining information concerning the study and providing contact information for the trial coordinator. Interested and potentially eligible participants will be asked to contact the trial coordinator directly. Pamphlets will also be available in patient waiting rooms of participating hospital clinics and community clinics. Similar information will be advertised in local newspapers to enhance recruitment. The trial coordinator will provide details about the study and answer questions by phone. The coordinator will confirm eligibility including age, duration of symptoms and self-report walking ability. Walking ability will be assessed by the participants’ response to the question *“are you able to walk continuously for 30 min without the use of aids or without stopping to rest or stoop forward to alleviate your symptoms?*” Self-reported walking ability has been shown to be highly correlated (*r* = 0.80) to the self-paced walking test (SPWT) [31]. The SPWT is a validated objective measure of walking ability in LSS [31]. Only interested participants who respond “NO” and meet the other inclusion/exclusion criteria will be given an appointment for an intake assessment at the study site (Mount Sinai Hospital in Toronto Canada).

**Table 1 Tab1:** Inclusion and exclusion criteria

Inclusion criteria	
1. Age greater or equal to 50 years	
2. Clinical symptoms of back and/or radiating lower limb or buttock pain; fatigue or loss of sensation in the lower limbs aggravated by walking and/or standing and relieved by sitting.	
3. Intermittent or persistent pain without progressive neurological dysfunction	
4. Duration of symptoms and signs for more than 3 months	
5. Imaging confirmed spinal canal narrowing using MRI, CT scan, myelography or ultrasound	
6. Clinical signs and symptoms corresponding to segmental level of narrowing identified by imaging	
7. Patients with degenerative spondylolisthesis are included	
8. Not considered to be a surgical candidate (in the next 12 months) or patient unwilling to have surgery	
9. Able to perform mild-moderate exercise	
10. Able to walk without assistive devices for at least 20 m and less than 30 min continuously	
11. Able to give written informed consent and complete interviews and questionnaires in English.	
Exclusion criteria	

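### The covariates named for the adjusted primary analysis, hospital above all, are too many for about 38 expected responders: if all enter an ordinary logistic model, the odds ratio is inflated and its interval somewhat too narrow

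*Protocol article*

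**What the plan says.** In the protocol article, Statistical analysis first tests the primary outcome by an unadjusted Pearson chi-squared comparison of the proportions reaching the assumed important gain in walking distance. For potential confounding it then adds logistic regression and GEE models and names the covariates: "sex, education, perceived health status, dominant leg or back pain, and hospital". The next sentence says that these models control for baseline differences that randomization did not balance. Dichotomous secondary outcomes are to be handled in the same way. The section gives no coding for hospital, education or perceived health, and names no penalised or small-sample method.

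Source population says that participants consult "at one of seven hospitals and several community clinics in Toronto, Canada and the surrounding area". Recruitment adds: "Similar information will be advertised in local newspapers to enhance recruitment". Intake, the Group 1 programme and follow-up all take place at the one study site.

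Sample size gives the planning figures: "We estimate a total of 30 % of participants will achieve the estimated MCID in Group 2 and 60 % in Group 1"; "a power of 0.8, an alpha of 0.05 and an estimated drop-out rate of 20" per cent; and "a minimum of 52 participants per group is estimated to be required". It closes with "Our primary end point will be the 6-month follow-up".

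**The concern.** With one study site, hospital can differ between participants only as the place they were referred from. Entered as a category, it alone may use seven or more parameters in a trial that expects fewer than 40 responders. Maximum-likelihood logistic regression with so few events per parameter pushes a real effect away from 1 and understates its standard error. A hospital whose participants all respond, or none of whom do, has no finite coefficient.

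The adjusted odds ratio is what readers will take as the result freed of chance imbalance. If it sits well above the unadjusted odds ratio, the gap could be read as confounding removed when it is small-sample bias.

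**Working it through.** **Inputs from Sample size.** 30 % v 60 %, two-sided alpha 0.05, power 0.80, drop-out 20 %, 52 per group.

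**The plan's own figure.** The pooled-variance formula for two proportions is n = [1.96·√(2 × 0.45 × 0.55) + 0.8416·√(0.30 × 0.70 + 0.60 × 0.40)]² / 0.30² = (1.379 + 0.565)² / 0.09 ≈ 42.0 per arm. Allowing for drop-out, 41.97 / 0.8 = 52.5. The stated 52 is reproduced within rounding.

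**Planned effect.** (0.60/0.40) / (0.30/0.70) = 3.5.

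**Expected responders.** 52 × 0.8 = 41.6 evaluable per arm, and 41.6 × (0.30 + 0.60) = 37.4. With 42 per arm it is 37.8. So about 38.

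**Parameters, excluding the intercept.**
- Minimum coding: treatment 1 + sex 1 + dominant pain 1 + education 1 + perceived health 1 + hospital 7 (seven hospitals, with all clinics pooled as an eighth level) = 12, or 37.4/12 = 3.1 responders per parameter.
- Education at 3 levels and health at 5: 1 + 1 + 1 + 2 + 4 + 7 = 16, or 37.4/16 = 2.3.

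**Simulation.** 83 evaluable, 2,000 trials per row, covariates unrelated to response, Wald intervals. Assumed hospital shares run from 30 % down to 6 %. Type I error comes from runs with 45 % responding in both arms. The Monte Carlo standard error of a 5 % rate is √(0.05 × 0.95/2000) = 0.5 points.

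| 6-month model | Parameters | Median OR (true 3.5) | Mean SE / actual SD | Coverage | Type I error | Power |
|---|---|---|---|---|---|---|
| ML, hospital 8 levels | 12 | 4.47 | 0.57 / 0.63 | 92.7 % | 6.6 % | 78.5 % |
| ML, hospital 8 levels | 16 | 5.05 | 0.62 / 0.73 | 90.9 % | 7.7 % | 75.2 % |
| ML, no hospital | 5 | 3.80 | 0.50 / 0.53 | 94.3 % | 6.0 % | 78.9 % |
| ML, no hospital | 9 | 4.20 | 0.54 / 0.59 | 93.4 % | 5.4 % | 77.7 % |
| Firth, hospital 8 levels | 12 | 3.45 | 0.54 / 0.52 | 96.4 % | 3.4 % | 67.4 % |
| Firth, hospital 8 levels | 16 | 3.56 | 0.57 / 0.57 | 96.4 % | 2.5 % | 62.6 % |
| Firth, no hospital | 5 | 3.50 | 0.50 / 0.48 | 96.1 % | 4.9 % | 74.9 % |

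Other runs with 8 or 9 levels agree: at 12 parameters, median OR 4.4 to 4.5 and coverage 91 to 93 %; at 16, about 4.9 to 5.0 and 89 to 91 %. Hospital collapsed to two levels with one term per other covariate gives, by maximum likelihood, OR about 4.0, coverage about 95 % and type I error 5.2 %.

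**Runaway hospital coefficients.** These occur in about a third of trials. The rate depends on the assumed shares and coding: different runs gave 23 to 38 % and 40 to 55 %.

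**GEE.** Four follow-up visits, independence working correlation, robust standard errors, assumed latent correlation 0.5 to 0.8, hospital at 8 levels: median OR 4.0 to 4.6, coverage 91 to 94 %, type I error 6.1 to 6.9 %.

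**Source of the inflation.** Because the simulated covariates do not predict response, the conditional and marginal odds ratios are both 3.5. The excess is therefore small-sample bias, not the legitimate shift of a conditional odds ratio.

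**The case against.** The strongest reply is that the text does not commit to this model. The sentence after the list may mean that only imbalanced covariates enter, and that reading cannot be excluded. If hospital alone joined treatment, the median OR would be about 4.0 with 94.2 % coverage, though a runaway hospital coefficient would still appear in 34 % of trials. The harm is then smaller, not nil.

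The eight levels are also inferred. A two-level coding is compatible with the text and nearly removes the problem. Counting advertisement respondents as a ninth level is doubtful, since Inclusion and exclusion criteria has imaging supplied by the referring specialist. Coding and estimator are often left to an analysis plan. That stands as far as it goes, but the covariate set is stated here, and fitted at face value it asks too much of the sample.

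Four stronger readings are tempting and not supported:
- **That the primary result is compromised.** The chi-squared comparison, on which the sample size rests, is untouched.
- **That the adjusted model often cannot be fitted.** The infinite coefficients belong to hospital levels. In 3,000 simulated trials per setting at 12 parameters, the treatment coefficient was finite in every one.
- **That the model favours the programme whatever the truth.** With no effect the odds ratio is centred on 1, and only the modest type I inflation remains.
- **That adjusting for hospital gains nothing.** Sources range from surgeons to family physicians and chiropractors, so referral source may be prognostic. A simulation with covariates unrelated to response cannot show otherwise.

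**Conclusion.** The concern holds conditionally. If all five covariates enter a 6-month maximum-likelihood model with hospital at eight or more levels, a true odds ratio of 3.5 is typically reported as about 4.5 to 5.0, with interval coverage of about 90 to 92 %. Type I error is about 6 to 8 %. Hospital is the main cause, and finer coding of education and health adds to it. GEE over all visits is milder but not clean.

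This rests on the planned response rates and drop-out, and on three things the article does not give: the coding of hospital, its shares, and the category counts for education and perceived health. The damage is confined to the adjusted odds ratios, including those for dichotomous secondary outcomes handled the same way. It is worth correcting, but it does not threaten the primary test.

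**What to change.** In Statistical analysis, state that the adjusted 6-month logistic model is fitted by Firth's penalised likelihood, with hospital as study hospital versus any other source and one term each for education and perceived health. That makes six parameters: treatment, sex, dominant pain, education, health and hospital. State also whether all the named covariates enter or only some.

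Firth's method alone repairs the bias and coverage even with hospital at eight levels, so dropping hospital is not necessary. Collapsing it still helps: in the table, power by the Firth Wald test is 63 to 67 % with eight levels and 75 % in the five-parameter model without hospital.

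The cost is a sentence or two. Any referral-source effect would be adjusted for only coarsely, and the Firth Wald test is slightly conservative.

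### The primary outcome gets an unadjusted test and imbalance-driven adjusted models with no stated order, and baseline walking distance is not among the covariates

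*Protocol article*

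**What the plan says.** Under Sample size, a responder is defined by walking distance: "we will estimate it to be an improvement in walking distance from baseline of 30 % or more". The expected rates are stated: "We estimate a total of 30 % of participants will achieve the estimated MCID in Group 2 and 60 % in Group 1". The calculation uses "an alpha of 0.05", power 0.8 and 20 % drop-out, and gives 52 per group "to achieve significance using a two-tailed" comparison of two independent proportions. The time point is fixed: "Our primary end point will be the 6-month follow-up".

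Under Statistical analysis, the first sentence on the primary outcome reads "We will analyze the primary outcome (SPWT) by calculating the differences in proportions meeting the MCID using Pearson Chi Squared test", with 95 % confidence intervals. The next sentence says that, to deal with confounding, "logistic regression models and generalized estimation equation (GEE) methods will be used". It lists sex, education, perceived health status, dominant leg or back pain, and hospital. The sentence after that reads "These models will control for baseline differences not balanced by randomization".

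No sentence calls any of these analyses primary, confirmatory, supportive or sensitivity. Baseline SPWT distance, which is measured before randomisation (Table 2), is not on the list. For continuous secondary outcomes a 10 % change-in-coefficient rule selects covariates; for the binary primary outcome no selection criterion is given.

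**The concern.** Three things are left loose for one endpoint.

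- **Order.** The unadjusted test and the adjusted models are all planned unconditionally. The models are presented as dealing with confounding, so a reader could take either result as the trial's answer. A difference in proportions, a covariate-conditional odds ratio and an effect averaged over visits are different quantities and can disagree at the margin of significance.
- **Covariates.** Five are listed, but the models are also tied to whatever imbalance is observed, after a round of baseline significance tests. Part of the adjustment set would then be chosen from the data. In a randomised trial, what matters for precision is how strongly a covariate predicts outcome, not whether it happens to be unbalanced.
- **The missing covariate.** Response is defined relative to baseline distance, so baseline distance is an obvious candidate predictor, and it is not listed.

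At stake are a clear decision rule, a single effect measure and some power that is available at almost no cost.

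**Working it through.** **1. Reproduce the sample size.** Inputs from Sample size: p2 = 0.30, p1 = 0.60, two-sided alpha 0.05 (z = 1.960), power 0.80 (z = 0.842), drop-out 20 %. With pooled variance and no continuity correction:

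n = [1.960 × √(2 × 0.45 × 0.55) + 0.842 × √(0.30 × 0.70 + 0.60 × 0.40)]² / 0.30² = (1.379 + 0.565)² / 0.09 ≈ 42 per arm.

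42 / 0.8 = 52.5, so 53 against the stated 52: reproduced to within one participant per arm. With 42 evaluable per arm, power is 80.0 %; with 52 × 0.8 = 41.6 it is 79.6 %. The trial is sized on the unadjusted 6-month comparison of proportions.

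**2. Error rate if more than one analysis could support the claim.** For independent tests at 5 %, the chance of at least one false positive is 1 − 0.95² = 9.8 % for two and 1 − 0.95³ = 14.3 % for three. The tests here share data, so these are rough upper references.

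Simulation under no treatment effect gives the correlated case. There were nine scenarios with 3000 replicates each: eight with 42 per arm and one with 52. Inputs that the document does not give were assumed: response rate 0.30 or 0.45 in both arms, latent within-person correlation 0.3 to 0.8 over four follow-ups, covariate effect 0 to 1.0, and three hospital categories. The GEE used an independence working correlation and robust standard errors. Covariates were fixed in advance, so these figures do not include any effect of imbalance-driven selection.

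| Claim allowed on p < 0.05 from | False positives | Excess over chi-squared in the same scenario |
|---|---|---|
| Chi-squared at 6 months only | 4.6-6.4 % | none |
| Chi-squared or adjusted logistic | 7.1-9.2 % | 1.1-2.9 points |
| Those two or GEE effect at 6 months | 7.4-10.2 % | 1.4-3.9 points |
| Those two or GEE effect pooled over visits | 10.9-13.4 % | 4.6-7.1 points |

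The Monte Carlo standard error is about 0.4 to 0.6 points. Part of the excess over 5 % is small-sample behaviour of the tests themselves: the pooled GEE effect alone rejects in 5.9-7.2 % of null trials.

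**3. Is baseline distance likely to predict response?** The SPWT stops at 30 min (Primary outcome). At unchanged pace, a 30 % gain in distance needs 1.3 times the baseline time. A participant who walked longer than 30 / 1.3 = 23.1 min at baseline therefore cannot respond without walking faster. Baseline performance is linked to response through the endpoint's own definition.

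**4. Power of an adjusted risk difference.** Simulation with 42 per arm and true rates 0.30 and 0.60 compared a logistic model with group and baseline SPWT, standardised to a risk difference, with the chi-squared test.

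| Assumed latent correlation of baseline with response | Standardised risk difference | Chi-squared |
|---|---|---|
| 0 | 81 % | 82 % |
| 0.4 to 0.6 | 84-90 % | 82-83 % |

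The correlation is an assumption; the document gives no figure for it.

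**The case against.** A reader might infer that three co-equal tests are planned and that the 5 % error rate is therefore unprotected. The document does not support that. The chi-squared comparison is the one attached to the primary outcome, it comes first, and it matches the sample-size section in effect measure, sidedness and alpha. The time point is fixed at 6 months. The models enter under a stated purpose, control of confounding, and nothing says that they override the test or that any one of them suffices for a claim.

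Nor is it certain that there are three analyses. For continuous outcomes the article describes least-squares models estimated by GEE, which is one analysis. The primary-outcome wording can likewise mean logistic models fitted by GEE, giving one unadjusted test and one adjusted model. The 11-13 % figure needs a separate GEE effect pooled over visits, which is not the 6-month end point, as well as selective claiming.

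A condensed article may also leave the order of analyses to an analysis plan that is not shown. On its own, the absence of a label on the chi-squared test would be such a detail. All of this stands and limits the point.

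It does not reach the rest. The imbalance-based adjustment is something the article states, not something it omits. The covariate list is given and leaves out baseline walking distance. Those are choices made in the text, and they can be improved.

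**Conclusion.** The point holds in limited form. Read as a whole, the article implies that the 6-month chi-squared test decides the trial, and on that reading alpha is nominally 5 % (simulated 4.6-6.4 %). The risk is conditional: about 7-10 % if chi-squared, adjusted logistic or a 6-month GEE effect could each support the claim, and 11-13 % only if a pooled GEE effect could as well. These figures rest on the assumed response rates, correlations, covariate effects and hospital categories listed above.

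The firmer weakness is the adjustment strategy. It is partly chosen from observed imbalance and leaves out the baseline value of the outcome. A pre-specified analysis adjusted for baseline SPWT distance targets the same 6-month difference in proportions. It costs about one point of power if baseline is not prognostic, and gains from about one or two up to seven or eight points if the assumed correlation is 0.4 to 0.6. The change is worth making, but the trial's validity does not depend on it.

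**What to change.** In Statistical analysis:

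- Name one confirmatory analysis: the difference in the proportion of responders at 6 months, with its 95 % CI and two-sided test at 0.05. Preferably obtain it from a logistic model with group and a short covariate list fixed in advance that includes baseline SPWT distance, standardised to a risk difference. At minimum, state that the Pearson chi-squared test is decisive.
- Delete the link between adjustment and observed baseline imbalance for the primary outcome.
- State that any GEE contrast for the primary outcome is the group effect at 6 months.
- State that all other primary-outcome models are supportive and cannot change the conclusion.

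Cost: a few sentences, no new data (baseline SPWT is already collected) and no change to 52 per group. The downside is slightly more analysis work and a negligible loss of power if the covariates turn out not to be prognostic.
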